## Abstract

**Introduction:**

Electroconvulsive therapy (ECT) is an effective intervention for patients with major depressive disorder (MDD). Despite longstanding use, the underlying mechanisms of ECT are unknown, and there are no objective prognostic biomarkers that are routinely used for ECT response. Two electroencephalographic (EEG) markers, sleep slow waves and sleep spindles, could address these needs. Both sleep microstructure EEG markers are associated with synaptic plasticity, implicated in memory consolidation, and have reduced expression in depressed individuals. We hypothesize that ECT alleviates depression through enhanced expression of sleep slow waves and sleep spindles, thereby facilitating synaptic reconfiguration in pathologic neural circuits.

**Methods:**

Correlating ECT Response to EEG Markers (CET-REM) is a single-center, prospective, observational investigation. Wireless wearable headbands with dry EEG electrodes will be utilized for at-home unattended sleep studies to allow calculation of quantitative measures of sleep slow waves (EEG SWA, 0.5–4 Hz power) and sleep spindles (density in number/minute). High-density EEG data will be acquired during ECT to quantify seizure markers.

**Discussion:**

This innovative study focuses on the longitudinal relationships of sleep microstructure and ECT seizure markers over the treatment course. We anticipate that the results from this study will improve our understanding of ECT.

## Highlights

-Electroconvulsive therapy (ECT) is a highly effective treatment for depression.-It is unclear how ECT perturbs brain circuitry.-There are currently no objective markers to prognosticate the likelihood of ECT response.-Assessing longitudinal changes in sleep microstructure–sleep slow waves and sleep spindles–may aid in elucidating neuroplasticity during the ECT course.-We hypothesize that ECT alters expression of sleep spindles and sleep slow waves to facilitate synaptic neural reconfiguration.-We will evaluate the following markers acquired throughout the ECT course: (1) sleep EEG markers from at-home sleep studies and (2) high-density EEG acquired during generalized seizures that can be localized to neural circuits.

## Introduction

### Electroconvulsive therapy: An effective treatment for depression but with unclear underlying mechanisms

Electroconvulsive therapy (ECT) is an effective treatment for major depressive disorder (MDD), a common illness ranking as the second leading cause of disability worldwide (1). During ECT, a brief electrical stimulus is delivered through the scalp to elicit a generalized seizure under general anesthesia. Two to three ECT sessions are administered per week during the index treatment course. Compared to oral antidepressants, ECT ameliorates depressive symptoms rapidly; some individuals experience improvement shortly after the third treatment (2). The response rate to ECT for a depressive episode is up to 80% (2–4), with remission rates ranging from 50 to 63% (5, 6).

Electroconvulsive therapy was used for the first time on a human patient in 1938 by Cerletti and Bini (7). Although ECT has been used for over 80 years, many unknowns remain. It is thought that ECT induces neuroplasticity and alters neural connectivity within functional networks; however, these networks have yet to be elucidated (8, 9). Moreover, it remains unclear why certain patients do not respond to therapy. Prognostic physiologic biomarkers are not routinely used to predict and monitor ECT response. Identifying such biomarkers may aid clinicians in referring the right candidates for ECT or adapting ECT parameters (i.e., charge and electrode placement) to improve treatment response.

### Probing relationships between sleep abnormalities and major depressive disorder

Sleep disturbance is prevalent in those with depression (10). Greek physicians in the 1600s described the co-occurrence of insomnia and depression in the *Anatomy of Melancholia* (11), as did the founder of modern psychiatry, Kraepelin, in the early 1900s (12). Between 60 and 90% of patients with MDD are afflicted by symptoms of delayed sleep onset, shorter sleep duration, and nonrestorative sleep (13, 14). Those with severe MDD sub-types and increased suicidal ideation are more likely to have poor sleep patterns (15). Similarly, individuals with sleep disturbances are at a higher risk of developing depressive symptoms (16).

Given this interaction between abnormal sleep and depression, previous investigations have relied on polysomnography (PSG) to study sleep patterns. PSG utilizes electroencephalography (EEG) and other physiologic signals to segment sleep into periods of rapid eye movement (REM) and stages of non-rapid eye movement (NREM) sleep (17). NREM stage 2 (N2) constitutes most of total sleep, while NREM stage 3 (N3/slow wave sleep) is associated with restorative physiologic benefits across multiple organ systems (18–20). Patterns of sleep disturbance associated with MDD, such as increased REM duration and shortened REM latency (21–23), have been considered as potential targets for monitoring antidepressant response (24).

Polysomnography usage in longitudinal studies has the following limitations: requirement of wire electrodes and sensors for monitoring; perturbations in natural sleep that may occur in a foreign environment, such as a sleep clinic; and limited scalability for large clinical study designs. Newer technology can circumvent such logistical impediments of PSG to allow longitudinal assessment of sleep structure over the course of ECT. The Dreem device (Figure 1A, Dreem, Paris, France) is a consumer-grade, wireless, dry-electrode headband that records EEG without the need for a continuous internet or Bluetooth connection (25). This device has previously been validated against polysomnography for monitoring sleep-related physiological signals and accurate sleep staging across broad age demographic (26). As the device has been suitable for longitudinal use in the perioperative setting (27), the Dreem device may be a feasible option for obtaining continuous sleep EEG data over an ECT course.

**FIGURE 1 F1:**
[figure not shown]
Dreem device and example illustration of sleep slow wave activity (SWA) and spindles. **(A)** The Dreem device is a consumer-grade, wireless EEG device. The device has three frontal EEG channels, at F7, F8, and Fpz, and two occipital channels at O1 and O2. Both frontal and occipital channels are sufficient to allow quantification of SWA (average power in 0.5–4 Hz frequency band per minute) and sleep spindle density (number of spindles a minute). **(B)** Slow waves (0.5–4 Hz frequency) and **(C)** sleep spindles (11–16 Hz frequency band).

### Sleep electroencephalographic markers of depression, antidepressant response, and synaptic plasticity

Two sleep EEG markers of synaptic plasticity, sleep slow waves, and sleep spindles, are pertinent to depression and antidepressant response.

Sleep slow waves (Figure 1B) are high-amplitude low-frequency oscillations (<4 Hz) with predominance during N3 sleep. Sleep slow wave activity (SWA) is quantified as the EEG power per minute in the 0.5–4 Hz frequency band. SWA is a physiologic marker of the homeostatic sleep pressure, as SWA increases during the day and decreases during NREM sleep (28–30). SWA during N3 sleep is reduced in the first cycle of sleep in depressed individuals versus healthy controls (31–33). Additionally, sleep slow waves may have a lower amplitude in patients with depression compared to healthy controls (34). Dissipation of SWA, measured as the decline of SWA throughout sleep, may also be an important marker. The delta sleep ratio (DSR; quotient of SWA during first N3 cycle SWA to SWA during the second N3 cycle) is low in patients with depression (35, 36).

Antidepressant therapies such as ketamine and sleep deprivation enhance subsequent sleep SWA in depressed individuals. Duncan et al. demonstrated that SWA in the first N3 cycle increased after subanesthetic ketamine infusion and was correlated with an improvement in depressive symptoms (37, 38). Sleep deprivation, which can confer short-lived antidepressant effects in a subset of MDD patients, leads to a subsequent rebound of sleep SWA (39), with a high DSR predicting antidepressant response (36). Altogether, these findings suggest that sleep SWA measures could be useful in monitoring antidepressant response.

Slow wave activity has also been linked to neural plasticity (40, 41), a key neuronal adaptation mechanism putatively impaired in depression (42–44). In rodents, expression of sleep SWA correlates with extent of environmental exploration (45), with sleep SWA augmented by exogenous brain-derived neurotrophic factor (BDNF) (44). BDNF is involved in the control of synapse formation and regulation (46–48), and its dysfunction leads to synaptic plasticity malfunction (49, 50). Neural plasticity involves changes in synaptic connections or remodeling of dendrites. Loss of dendritic branching and spine complexity have been shown in human postmortem hippocampal tissue in depressed individuals (51). These impairments in neuroplasticity have been rescued by rapid antidepressants *via* the neurotrophic cascade (52). Sleep may be an important time for this synaptic remodeling of connections built during the wakeful conscious experience (53) with sleep SWA as a marker of net cortical synaptic strength. Facilitation of synaptic plasticity in memory reconsolidation involves temporal coordination of sleep slow waves and sleep spindles (54–57).

Sleep spindles (Figure 1C) are 11–16 Hz crescendo-decrescendo oscillatory signatures that define entry into N2 sleep. Sleep spindles originate from circuits that include the thalamic reticular nucleus and the neocortex (58). Spindles are hypothesized to stabilize sleep and are associated with consolidation of memory during sleep (59–62). It is hypothesized that depression is linked to poor memory for positive stimuli, leading to a void of positive memories and anhedonia (63). Moreover, individuals with MDD have impairments in memory consolidation (64) and a reduction of spindle density, defined as the number of detected spindles per minute (65, 66). Decreased sleep spindle density is also observed in response to stress (67). While decreased spindle density is associated with depression, it remains unclear if and how antidepressants regulate sleep spindles.

Given the interrelatedness among SWA, sleep spindles, depression, and neuroplasticity (68), it is plausible that SWA and sleep spindles may serve as biomarkers of synaptic reconfiguration induced during responses to ECT and other antidepressants (29).

### Electroconvulsive therapy alters sleep macrostructure, but changes in sleep microstructure remain uncharacterized

A few studies have examined longitudinal changes in sleep architecture in response to ECT. These have focused on measures of sleep macrostructure, including durations or latencies of REM or N3 sleep. Most studies have examined ECT-induced changes in sleep EEG by comparing sleep macrostructure before and after an entire treatment course, with discordant results. A full course of ECT is associated with increases in daytime activity, total sleep time, and sleep efficiency (69). Right unilateral ECT increased the proportion of REM and N3 sleep in a group of 15 adult patients who showed remission from depression (70). However, another set of studies reported no significant association between REM sleep parameters when comparing ECT responders and non-responders (71–73). One concern is that sleep macrostructure markers are impacted by variability in daytime somnolence and artifacts that impair sleep staging. In contrast, sleep SWA and sleep spindle density are quantitative EEG metrics that may be more robust to such sources of variance. How sleep spindle density or sleep SWA evolves over an ECT course remains unknown.

### Electroconvulsive therapy induces seizure markers linked to sleep circuitry

While induction of a seizure is required for an antidepressant response, criteria for an efficacious seizure remain unknown. Initially, longer seizure duration was associated with increased effectiveness; however, this relationship has not held (74, 75). Thus, there is growing interest in identifying objective seizure quality markers for prognosticating clinical outcomes. Several EEG characteristics have been employed to predict response to ECT, including postictal suppression (76, 77) and ictal amplitude measures (78). Yet, such EEG measurements have not been integrated into clinical practice as biomarkers of ECT efficacy (79).

Through evaluation of high-density EEG acquired during right unilateral ECT (Figure 2A) (80), our group detected an ECT-induced ictal wave form during associated generalized seizures. These central-positive complexes (CPC) (81) are large in amplitude (hundreds of microvolts) with a descending gradient of positive electrical charge from the vertex of the scalp (Figure 2B). During ECT-induced seizures, CPCs correlate with bilateral clonic activity, qualitatively decreasing in frequency over time (81). Peak amplitude of CPCs are localized to the cingulate cortex and medial dorsal thalamus (82)—structures involved in the formation of sleep slow waves and sleep spindles (64, 83–85). Thus, CPCs could be involved in the alteration of SWA and sleep spindles, but the relationships between CPCs, sleep slow waves, and sleep spindles throughout treatment course requires further elucidation.

**FIGURE 2 F2:**
[figure not shown]
High-density EEG during ECT and evaluation of CPCs. **(A)** A modified high-density 64-electrode EEG net with right unilateral ECT placement (ECT paddles marked with asterisks). **(B)** Data from a single seizure, during phase 3 and 10 s after seizure termination, is shown. EEG amplitude between Cz and suborbital facial electrodes (Cz-Face) is used to detect large amplitude CPCs. Green line shows seizure termination and onset of postictal generalized EEG suppression (PGES) (103, 104). Topographic maps represent spatial topology of EEG voltage during phase 3 (red arrow) and PGES (blue arrow).

### Objectives and specific aims

The primary objective of our study is to longitudinally track changes in sleep microstructure throughout the ECT course of a convenience sample of patients, who are clinically ascertained and treated for depressive episodes on a busy hospital-based service. Wearable dry-electrode EEG devices will be utilized to monitor overnight sleep at home. High-density EEG during the ECT procedure will allow characterization of seizure markers. Specific aims, hypotheses, and analytical approaches are listed below.

#### Specific aim 1

Assess changes in N2 and N3 sleep SWA over the course of serial ECT sessions. We hypothesize SWA will increase over the course of ECT. Separate linear mixed effects models will be constructed to assess SWA changes in responder and non-responder groups.

#### Specific aim 2

Evaluate changes in sleep spindle density during N2 and N3 sleep over the course of ECT. We predict that there will be an increase in sleep spindle density throughout ECT. Separate linear mixed effects models will be constructed to assess changes in sleep spindle density in responder and non-responder groups.

#### Exploratory aim

Characterize the relationship between changes in CPCs and sleep SWA and spindle density. We hypothesize that the cumulative duration of CPCs will positively correlate with SWA and sleep spindle density. Separate linear mixed effects models will be constructed to test this hypothesis in responder and non-responder groups.

## Methods and analysis

### Study design

Correlating Electroconvulsive Therapy Response to Electroencephalographic Markers (CET-REM) is a single center, prospective, observational study (ClinicalTrials.gov: NCT04451135) in a clinically ascertained and treated sample. See Figure 3 for study design. Inclusion criteria include planned ECT, age 18 and above, presence of a depressive episode (either unipolar or bipolar depressive episode). Exclusion criteria include schizophrenia and schizoaffective disorder.

**FIGURE 3 F3:**
[figure not shown]
PICOT (participants, intervention, control, outcomes, timing) summary of study design. This study will recruit adults requiring ECT treatment for a depressive episode. Participants will wear a Dreem headband at night to obtain sleep EEG recordings throughout the course of ECT. High-density EEG recordings will also be obtained during ECT sessions to assess central positive complexes (CPCs). The primary outcomes of CET-REM include characterization of slow wave activity and sleep spindle density throughout ECT course.

Each enrolled participant will undergo an index course of ECT, following standard clinical care. Self-reported depressive scores will be assessed prior to each ECT session to determine response, and the total number of treatments will be determined by the psychiatrist performing ECT, as part of routine clinical practice. Response to the ECT will be defined as a 50% reduction of baseline QIDS score. Sleep structure on the nights of ECT sessions would be confounded by the effects of the anesthetic used in the procedure. Thus, ambulatory overnight sleep EEG data will be acquired *via* a Dreem device on post-ECT days. For exploratory analyses, optional high-density EEG data will be recorded during ECT-induced seizures. Our study design will allow us to longitudinally collect a large data set of EEG markers, including sleep slow waves, sleep spindles, and CPCs.

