### Clinical assessments

Two clinical assessments will be done throughout this study, the QIDS-SR16 (Quick Inventory of Depressive Symptomatology-16 Self Report), and the PSQI (Pittsburgh Sleep Quality Index). The QIDS-SR16 measures the participant’s depressive symptoms over the past seven days (86). At our institution, patients receiving ECT typically complete QIDS-SR16 throughout their ECT course. While other scales for measuring depression severity exist, such as Hamilton Depression Rating Scale (HAMD) and Montgomery–Asberg Depression Rating Scale (MADRS), the usage of QIDS-SR16 in the ECT suite has been historically chosen because it is a patient-reported assessment that accommodates for the high volume of participants in the suite limited clinician resources. The questionnaire includes 16 questions that survey nine symptom domains: sad mood, self-criticism, poor concentration, suicidal ideation, anhedonia, energy, sleep disturbance, appetite, and psychomotor agitation. Paper versions of the QIDS-SR16 will be completed by participants prior to each ECT session. The PSQI is a scoring system to assess sleep quality and habits during the past month (87). The assessment measures seven components of sleep: subjective sleep quality, sleep latency, sleep duration, sleep efficiency, sleep disturbances, sleeping medications, and daytime dysfunction. PSQI will be obtained *via* an electronic form administered prior to the first ECT session. Suicidality will be assessed by psychiatry physicians in the ECT suite, as per standard of care.

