### Statistical analysis

Linear mixed-effects models will be constructed to account for missing data without the need for data imputation or deletion. Models will be generated in MATLAB. To characterize SWA over the course of ECT, linear mixed-effect models will be constructed using SWA as a dependent variable and treatment number as an independent variable. Similarly, to examine sleep spindle density changes, linear mixed-effects models will be generated that have sleep spindle density as a dependent variable and treatment number as an independent variable. Associations between CPC and sleep SWA or sleep spindles will be evaluated *via* respective linear mixed-effect models. For all aims, separate models will be constructed for responder and non-responder groups. QIDS-SR16 scores and ECT stimulation *parameters* will be entered as covariates for all analyses, as appropriate.

A total number of 25 participants will be targeted for recruitment in this study. Sample size calculations are based on the published data following conventions for statistical power analysis in the behavioral sciences (100) and our best guesses regarding effect size and SD. The main factor that we considered in estimating our required sample size was based on reported changes in SWA measure in major depression (98, 101, 102). We estimate a medium effect size and a partial η^2^ value of 0.1. Thus, we estimate sample sizes of 17 (power of 0.8, alpha of 0.05) based on a conservative assumption on the number of treatments (10 treatments) to account for missing a session or poor quality of EEG data. Participants may withdraw from the study at any time, and we will track reasons for patient attrition. Given that a previous study on a similar patient population cohort conducted at Barnes-Jewish Hospital and Washington University showed a 30% attrition rate (80), we expect to have at least 17 participants with interpretable data in the current study.

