## Conclusion

The CET-REM study will probe longitudinal changes in sleep microstructure and seizure markers over the index course of ECT. Wireless wearable devices will be utilized for at-home unattended collection of sleep EEG to provide measures of sleep slow waves and sleep spindles. ECT-induced seizure markers will be assessed using high-density EEG recordings. Overall, the results from this study will elucidate underlying mechanisms and markers for responsiveness to ECT.

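### ECT response is used only as a 50% QIDS-SR16 cut that splits every model, so any link between sleep EEG change and response loses about 36% to 51% of its information

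*Protocol article*

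**What the plan says.** Under Study design, in the text after the Figure 3 legend, the article defines response: "Response to the ECT will be defined as a 50% reduction of baseline QIDS score". Under Statistical analysis it applies that definition throughout: "For all aims, separate models will be constructed for responder and non-responder groups". Objectives and specific aims repeats the split for both specific aims and for the exploratory aim.

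The model for slow wave activity is given as follows: "linear mixed-effect models will be constructed using SWA as a dependent variable and treatment number as an independent variable". The spindle model has the same form. Neither contains a stated term for the degree of improvement or for response by treatment number.

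The graded score is available: "Paper versions of the QIDS-SR16 will be completed by participants prior to each ECT session" (Clinical assessments). It also has one other role in the analysis: "QIDS-SR16 scores and ECT stimulation *parameters* will be entered as covariates for all analyses, as appropriate".

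The study is named for correlating ECT response with EEG markers, and the Conclusion says that "the results from this study will elucidate underlying mechanisms and markers for responsiveness to ECT".

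**The concern.** The scale on which response is used does not suit what the study hopes to say about it. A participant who improves by 49% and one who improves by 51% are put in different groups, while 51% and 95% improvers are treated as alike. With about 17 evaluable participants there is little information to spare. At stake is the statement about markers of responsiveness: an association between EEG change and improvement is easier to miss after the cut.

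This differs from asking whether the two groups are formally compared. A formal comparison of responders with non-responders would still carry the same loss.

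**Working it through.** **Inputs.** From Statistical analysis: 25 recruited, 30% attrition, 17 evaluable, power 0.8, alpha 0.05, partial η² 0.1, 10 treatments. From the Introduction: "The response rate to ECT for a depressive episode is up to 80" per cent; the 50 to 63% given beside it are remission rates. Assumed here: response rates of 50%, 63% and 80%; a normally distributed QIDS change; a linear relation to each participant's EEG slope; a true correlation r of 0.4, 0.5 or 0.65.

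**The plan's own figure.** Take a one-group repeated-measures F test under sphericity, with f² = 0.1/0.9 = 0.111 and λ = f² × N × (m − 1) = 0.111 × 17 × 9 = 17.0, on 9 and 144 degrees of freedom. Power is 0.81 at N = 17, so the stated size reproduces under this convention (other common conventions for λ with the same inputs and uncorrelated repeats give 16 or 18). Attrition: 17/0.7 = 24.3, rounded up to 25. The figure is for change over treatments in one undivided group. It does not address the link to response.

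**Expected split of 17.** 8.5/8.5 at 50% response, 10.7/6.3 at 63%, 13.6/3.4 at 80%. The chance of three or fewer non-responders is 0.006, 0.08 and 0.55 respectively (0.20 at 70%).

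**Loss from the cut.** When a normal variable is cut so that a share p are responders, its correlation with another variable is multiplied by φ(z_p)/√(p(1 − p)), where z_p is the normal quantile of p. The share of R² kept is the square of that factor.

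| Responders | Factor on r | R² kept | Loss | 17 participants worth |
|---|---|---|---|---|
| 50% | 0.80 | 0.637 | 36% | 17 × 0.637 = 10.8 |
| 63% | 0.78 | 0.612 | 39% | 17 × 0.612 = 10.4 |
| 80% | 0.70 | 0.490 | 51% | 17 × 0.490 = 8.3 |

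**Power at N = 17**, two-sided 0.05, by simulation: correlation test on the continuous change against a two-group t test after the cut.

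| Assumed r | Continuous | Cut, 50% | Cut, 63% | Cut, 80% |
|---|---|---|---|---|
| 0.4 | 0.37 | 0.24 | 0.23 | 0.18 |
| 0.5 | 0.56 | 0.37 | 0.36 | 0.27 to 0.28 |
| 0.65 | 0.85 | 0.62 | 0.60 | 0.45 |

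**Does the QIDS covariate recover the loss?** No. It is entered only where judged appropriate, and inside groups already formed on QIDS change, so its range is restricted. As a main effect it adjusts the level of the EEG measure. Whether the EEG slope over treatments varies with improvement is tested only by an interaction with treatment number across all participants, and none is stated.

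**The case against.** The strongest reply is that the primary objective is change in sleep EEG over the course, with EEG as the dependent variable and treatment number as the independent variable. No between-person correlation with QIDS change is hypothesised and no between-group test is stated, so the power figures above belong to no planned test. That stands as a limit on what they mean: they show the cost to any inference about response drawn from the cut. They are not the power of a planned test. It does not remove the point, because the plan runs every aim by responder status and promises markers of response.

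A second reply is that a 50% reduction is a familiar definition and keeps results comparable with the responder language of the article's background. That is a good reason to display the split. It is not a reason to make it the only scale on which response is analysed. A third is that a fuller plan may say how QIDS enters. It may, but the split itself is stated outright for all aims.

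Three stronger readings are tempting and are not supported:

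- **That the cut discards most of the information.** The loss passes one half only at about 79% responders or more, and 80% is quoted as a ceiling. The 0.55 chance of three or fewer non-responders belongs to that same ceiling.
- **That the plan's own effect size sets the power of the response link.** "We estimate a medium effect size and a partial η^2^ value of 0.1" concerns change over treatments. Taking its square root, 0.316, as a between-person correlation changes the quantity being estimated.
- **That the graded score is dropped altogether.** It is planned as a covariate.

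**Conclusion.** The point holds as a cheap improvement. Response status enters the plan only as a yes/no cut, and that cut divides every model. Across assumed response rates of 50% to 80%, it costs about 36% to 51% of the information on any link between EEG change and response. At an assumed correlation of 0.5, power falls by roughly 19 to 29 points.

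The figures rest on a normal response variable, a linear relation, 17 evaluable participants, and response rates of which only the upper end comes from the article. The assumed correlations have no source in the document. The stated sample size is not in error on this account.

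**What to change.** For the link to response in Aims 1 and 2, fit one mixed model over all participants. Include each participant's continuous QIDS-SR16 change (percent, or absolute with baseline adjustment), treatment number and their interaction. For the exploratory aim, use the interaction of QIDS-SR16 change with CPC duration. Say whether the session-level QIDS covariate stays in this model, since it carries part of the same information. Keep the 50% responder and non-responder results as a descriptive display.

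The cost is analysis wording only, because the score is already collected before each session. There are two small downsides. The model assumes a roughly linear relation, which should be checked, all the more as the Limitations section itself warns of nonlinearity. And power for the response link stays modest at 17 participants, so the result should be reported as an estimate with its interval.
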